**6.1 Ethics review**

The entire study protocol, including informative material for the patients and modules for the informed consent, will be evaluated by the Ethics Committee (EC) of the National Institute for Infectious Diseases “Lazzaro Spallanzani”, Rome, Italy, which is the National Ethics Committee for evaluation of clinical trials on human drugs in COVID-19 patients. The study will not start before obtaining a favourable opinion from the EC, the Competent Authority Authorization and any other authorization required by local regulation. Every intention to modify any element of the original protocol after the first approval will be promptly notified to the EC and will be applied only after its written authorization.

Investigators will be responsible for submitting any amendments to the protocol to the EC.

Any modifications to the protocol which may impact on the conduct of the study, may affect patient safety, including changes of study objectives, study design, patient population, sample size, study procedures or significant administrative aspects will require a formal amendment to the protocol. Such amendments will be agreed and approved by the Ethics Committee of the National Institute for Infectious Diseases “Lazzaro Spallanzani”, Rome, Italy, as the National Ethics Committee for evaluation of clinical trials on human drugs in COVID-19 patients and the health authorities prior to implementation, in accordance with local regulation. Administrative changes of the protocol are minor corrections and/or clarifications that have no effect on the way the study is to be conducted. These administrative changes will be documented in a memorandum.

**6.2 Ethical conduct of the study**

The study was designed and will be implemented and performed in accordance with the ICH Harmonized Tripartite Guidelines for Good Clinical Practice, with applicable local regulations (including European Directive 2001/20/EC), and with the ethical principles laid down in the Declaration of Helsinki.

- 1. **Written informed consent**

The Investigator at each Centre will ensure that the subject is given full and adequate oral and written information about the nature, purpose, possible risks and benefits of the study. Subjects must also be notified that they are free to discontinue from the study at any time. The subject’s signed and dated informed consent must be obtained prior to conduct any procedure specific for the study. The original signed Written Informed Consent Form must be stored, and a copy must be given to the patient.

- 1. **Subject data protection**

The Written Informed Consent Form will explain that the study data will be stored on a centralised hospital server, maintaining confidentiality in accordance with national data legislation. The Investigator must ensure anonymity of the patients; all computer data will be identified by subject initial and number only. Enrolment log must be kept strictly confidential to enable patient identification at the site.

- 1. **Audits and inspections**

The Principal Investigator and the SC will provide all the necessary information and material to the participating centres in order to standardize all the protocol-related procedures and to avoid unexpected variability between centres. A preliminary audit between the CC and the satellite centres will be performed before starting the recruitment phase to offer as much consensus and homogeneity as possible. Printed and electronic informative material (complete original protocol, informed consent modules, informative modules for patients and relatives, recruitment checklist, graphic timeline of interventions and visits, order list for physicians and nurses) will be distributed to every Centre.

Source data/documents must be available to inspections by the designee or Health Authorities.

- 1. **Declaration of interest**

The study participants declare no financial and/or other conflicts of interest related to the study.

- 1. **Dissemination policy**

The Circ. Min. Health N° 6 of 09/02/2002 obliges each researcher who gets any results of interest to public health, to publish the results within 12 months from the end of the study. All the patients will freely agree or disagree to participate in the study in the belief that the results will be useful to improve knowledge about their pathologies, for health benefit from themselves or other patients. To respect their will and in the maximum interest of honest clinical research, the investigators agree on the need to ensure the wide publication and diffusion of their results in a consistent and responsible way under their responsibility. The Study Coordinator is the official data owner. The Study Coordinator has the right to present methods and results of the study at public symposia and conferences. The principal publications from the trial will be in the name of Investigators with full credit assigned to all collaborating investigators and institutions.

**APPENDIX 2: Timeline-scheme**

| Required investigations or activities | Screening | For any treatment | | | | | | | |  |
| --- | --- | --- | --- | --- | --- | --- | --- | --- | --- | --- |
|  | Within 5 days | Day 1 | Day 2 | Day 3 | Day 4 | Day 5 | Day 7 | Day 8 | Day 9 up to hospital discharge,  or up to occurrence of death | Day 30  Only for patients discharged from hospital before 30 days |
| Clinical history | x | x |  |  |  |  |  |  |  |  |
| Informed consent Form | x |  |  |  |  |  |  |  |  |  |
| **Physical exam** | x | x | x | x | x | x | x | x | x |  |
| **Vital signs*** | x | x | x | x | x | x | x | x | x |  |
| Body weight | x |  |  |  |  |  |  |  |  |  |
| Height | x |  |  |  |  |  |  |  |  |  |
| **Performance status** | x | x |  |  |  |  |  |  | x |  |
| Eligibility criteria | x |  |  |  |  |  |  |  |  |  |
| Pregnancy Test | x |  |  |  |  |  |  |  |  |  |
| Randomization |  | x |  |  |  |  |  |  |  |  |
| **Concomitant medications** | x | x | x | x | x | x | x | x | x |  |
| **Lab Tests**** | x | x | x |  | x |  | x |  | x |  |
| **Enoxaparin (Low-Dose LMWH) every 24 hours** |  | x | x | x | x | x | x | x | x |  |
| **Enoxaparin (High-Dose LMWH) every 12 hours** |  | x | x | x | x | x | x | x | x |  |
| **Health monitoring** |  | x | x | x | x | x | x | x | x | X **^⊥^** |

* systolic and diastolic arterial pressure, heart rate (HR), respiratory rate (RR) and systemic body temperature

** blood cells count, coagulative parameters (INR, PT, aPTT, fibrinogen, D-dimer), parameters for liver (AST, ALT, bilirubin) and renal function (creatinine) and interleukin 6 (IL-6) will be recorded at least at the moment of randomization, after 48 and 96 hours, then according to clinical judgement of the attending physician until to hospital discharge

**^⊥^** Information about these patients will be sought by phone call

**APPENDIX 3: Sepsis Induced Coagulopathy (SIC) score**^1^

| Category | Parameter | 0 point | 1 point | 2 points |
| --- | --- | --- | --- | --- |
| Prothrombin time | PT-INR 4 | <1.2 | >1.2 >1.4 | >1.4 |
| Coagulation | Platelet count (x10^9^/L) | > 150 | < 150 | <100 |
| Total SOFA | SOFA 4 items (respiratory,  cardiovascular, hepatic, renal | 0 | 1 | >2 |

**APPENDIX 4: Sequential Organ Failure Assessment (SOFA) score**^1^

| Variables | 0 | 1 | 2 | 3 | 4 |
| --- | --- | --- | --- | --- | --- |
| Central Nervous System  (Glasgow Coma Scale score) | 15 | 13-14 | 10-12 | 6-9 | <6 |
| Respiratory  (PaO_2_ / FiO_2_ ratio) | >400 | ≤ 400 | ≤ 300 | ≤ 200 ^A^ | ≤ 200 ^A^ |
| Cardiovascular, Hypotension  (MAP; mmHg / catecholamine dose; γ/Kg/min) | PAM >70  and NO cathecolamines | PAM < 70  and NO cathecolamines | Dop^B^≤ 5  or  Dob^B^ (any dose) | Dop^B^>5  or  Epi^B^≤0,1  or  Norepi^B^≤0,1 | Dop^B^> 15  or  Epi^B^>0,1  or  Norepi^B^> 0,1 |
| Coagulation  (Platelets ; x 10^3^ u/μL) | >150 | ≤ 150 | ≤ 100 | ≤ 50 | ≤ 20 |
| Liver  (Bilirubin; mg/dl) | <1,1 | 1,2 - 1,9 | 2,0 - 5,9 | 6,0 – 11,9 | >12 |
| Renal  (Creatinine; mg/dl  /diuresis ;ml/24h) | <1,1  +  diuresis > 500 | 1,2 - 1,9  +  diuresis > 500 | 2,0 - 3,4  +  diuresis > 500 | 3,5 – 4,9  or  diuresis <500 | >5  or  diuresis <200 |

A - Values are with respiratory support.

B – Cathecolamines are specified as follow:

| Dop | Dopamine |
| --- | --- |
| Dob | Dobutamine |
| Epi | Epinephrine |
| Norepi | Norepinephrine |

1. Vincent, J. L. *et al.* The SOFA (Sepsis-related Organ Failure Assessment) score to describe organ dysfunction/failure. On behalf of the Working Group on Sepsis-Related Problems of the European Society of Intensive Care Medicine. *Intensive Care Med.***22,** 707–710 (1996).

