| **Statistical Considerations**  **& Sample Size** | **Statistical Considerations**  The efficacy will be assessed by estimating the difference between the two treatment arms in the proportion of participants experiencing clinical worsening during their hospital stay.  Safety will be assessed by estimating the difference between the two treatment arms in the proportion of participants who experience at least one bleeding event (major or non-major) during their hospital stay.  Relative risk (RR) will be used as measure of association, which will be reported with its 95% confidence interval.  The differences between the two arms in the variation of:   1. D-dimer level 2. Plasma fibrinogen levels   3) Mean platelet Volume  4) Lymphocyte/Neutrophil ratio  5) IL-6 plasma levels  at 3 time points (at randomization, at 48 hours and 96 hours) will be assessed.  These outcomes will be compared by using their mean values and summary indicators.  Overall survival, survival free from any cardiovascular event, such as Acute Myocardial Infarction [AMI], Objectively confirmed, symptomatic arterial or venous thromboembolism [TE] and survival free from need for either non-invasive or invasive mechanical ventilation will be also estimated. They will be reported by using Kaplan-Maier curves and compared by using hazard ratio (HR).  **Sample size**  300 participants will be needed to detect a relative reduction of 50% of clinical worsening. We hypothesized that the percentage of participants who experience clinical worsening in the LMWH low dose group would be around 25-30% and set an alpha error of 0.05 and beta-error of 0.20. | |
| **Treatment Schedule** | **Control group (Low Dose):** Enoxaparin (Inhixa®) 4000 IU subcutaneously once daily.  **Intervention group (High dose**): Enoxaparin (Inhixa®) 70 IU/kg subcutaneously twice daily.  Participants will receive the dose of Enoxaparin according to the protocol until the occurrence of at least one of the following events:   1. One of the events included in the primary outcome 2. Hospital discharge 3. Any adverse events and clinical condition requiring interruption of the scheduled intervention according to the judgement of the physician in charge | |

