**Duration of follow-up**

Each patient will be followed-up until hospital discharge. Information about the status (dead/alive) of patients who are discharged from hospital before 30 days will be sought on Day 30 from randomisation.

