**2.4.3 Physiological and Processes of care outcomes**

- Vital signs such as systolic and diastolic arterial pressure, heart rate (HR), respiratory rate (RR) and systemic body temperature will be recorded daily from inclusion until hospital discharge (censored day 28);
- Routine laboratory test parameters for organ function assessment: blood cells count, coagulative parameters (INR, PT, aPTT, fibrinogen, D-dimer), parameters for liver (AST, ALT, bilirubin) and renal function (creatinine) and interleukin 6 (IL-6) will be recorded at least at the moment of randomization, after 48 and 96 hours, then according to clinical judgement of the attending physician until hospital discharge.

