**4.0 METHODS: DATA COLLECTION, MANAGEMENT, ANALYSIS AND MONITORING**

**4.1 Data collection and management**

Every patient who meets the inclusion criteria will be included and randomised in the two groups. The study data will be collected during the entire study period in a dedicated electronic Case Report Form (eCRF).

The eCRF will be provided by the Steering Committee (SC) with proper options to minimize data entry errors: the datasheet will incorporate un-amendable fixed intervals of values (for continuous variables) and pre-defined coding system (for binary or categorical variables). Data entry will be performed and double-checked by a dedicated team of researchers. Data will be collected and stored on the hospital server, which will be protected by password to prevent unintentional modification or deletion. Data related to the study will be stored for eventual further analysis or study purpose for 10 years after the end of the study.

All the data about the included patients will be recorded in an eCRF by trained researchers.

Demographic information, symptoms and co-morbidities, will be registered at the inclusion. During the study duration, the following clinical and laboratory parameters will be evaluated and recorded according to the timeline schedule reported in APPENDIX 2:

- Vital signs such as systolic and diastolic arterial pressure, heart rate (HR), respiratory rate (RR) and systemic body temperature will be recorded daily from inclusion until hospital discharge;

- Routine laboratory test parameters for organ function assessment: blood cells count, coagulative parameters (INR, PT, aPTT, fibrinogen, D-dimer), parameters for liver (AST, ALT, bilirubin) and renal function (creatinine) and interleukin 6 (IL-6) will be recorded at least at the moment of randomisation, after 48 and 96 hours, then according to clinical judgement of the attending physician until hospital discharge.

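### Appendix 2 marks the early laboratory tests on Day 2 and Day 4, but with randomisation on Day 1 the required 48 h and 96 h samples fall on Day 3 and Day 5, which are blank (minor)

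*Protocol*

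**What the plan says.** **The required times.** The synopsis (Statistical Considerations) says that between-arm differences in the variation of D-dimer, fibrinogen, mean platelet volume, lymphocyte/neutrophil ratio and IL-6 "at 3 time points (at randomization, at 48 hours and 96 hours) will be assessed". The section on physiological and process-of-care outcomes says the routine laboratory values "will be recorded at least at the moment of randomization, after 48 and 96 hours". The laboratory bullet in Section 4.1 repeats this: values "will be recorded at least at the moment of randomisation, after 48 and 96 hours". The footnote to the laboratory row in Appendix 2 gives the same minimum, with sampling "after 48 and 96 hours, then according to clinical judgement of the attending physician until to hospital discharge".

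**The grid.** The column headings in Appendix 2 run from Screening through Day 1, 2, 3, 4, 5, 7 and 8, then Day 9 onward, then Day 30. There is no Day 0. The randomisation row carries a single mark, under Day 1. The laboratory row is marked at Screening, Day 1, Day 2, Day 4, Day 7 and Day 9 onward. Day 3, Day 5 and Day 8 are blank.

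**The link between them.** Section 4.1 makes the grid an instruction to sites: "the following clinical and laboratory parameters will be evaluated and recorded according to the timeline schedule reported in APPENDIX 2".

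**The concern.** The two on-treatment samples that the analysis needs appear to be marked on the wrong days. With randomisation on Day 1, one would expect 48 h under Day 3 and 96 h under Day 5, and those are two of the cells left empty. The protocol states no day convention that would reconcile the marks with the hours.

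At stake is the timing of the secondary laboratory comparisons. Ten centres are expected to take part (Section 2.7). If some work from the marks and others from the footnote, values analysed as 48 h and 96 h would be a mixture of true and earlier times. That adds noise to markers measured early in treatment. If off-time samples were later set aside, values could also be lost, but the protocol states no sampling window, so that is only a possibility.

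**Working it through.** **Inputs**
- Randomisation: Day 1 only (Appendix 2, randomisation row).
- Early on-treatment laboratory marks: Day 2 and Day 4 (Appendix 2, laboratory row).
- Required times: 48 h and 96 h after randomisation (synopsis, process-of-care section, Section 4.1, footnote in Appendix 2).
- Delay from randomisation to first dose: at most 12 h (Section 2.3).

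**Step 1. Are the cells read correctly?** The laboratory, randomisation and vital-signs rows each have 10 cells, matching the 10 column headings. Other entries sit where they should, for example screening-only items under Screening. A column shift from the PDF is unlikely.

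**Step 2. On which day do the required times fall?** Let randomisation occur at clock hour t on Day 1, with 0 ≤ t < 24. The calendar day h hours later is

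day(h) = floor((t + h)/24) + 1.

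- h = 48: t + 48 lies in [48, 72), so the floor is 2 and the day is 3, for every t.
- h = 96: t + 96 lies in [96, 120), so the floor is 4 and the day is 5, for every t.

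The grid's Day 2 and Day 4 are not reproduced for any clock time.

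**Step 3. What elapsed time do the marked days give?** Calendar Day D covers 24(D − 1) − t to 24D − t hours after randomisation.

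| Marked day | Covers (hours) | Over all t | Same clock time | Required | Ratio |
| --- | --- | --- | --- | --- | --- |
| Day 2 | 24 − t to 48 − t | 0 to 48 | 24 h | 48 h | 24/48 = 50% |
| Day 4 | 72 − t to 96 − t | 48 to 96 | 72 h | 96 h | 72/96 = 75% |

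A draw on a marked calendar day is therefore never later than required. It comes close only when randomisation was early on Day 1 and the draw is late on the marked day. For a patient randomised at noon (t = 12, chosen for illustration), Day 2 spans 12 to 36 h and Day 4 spans 60 to 84 h.

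**Step 4. Does another reading rescue the marks?**
- *A day is a 24-hour period from randomisation.* Day 2 is then 24 to 48 h and Day 4 is 72 to 96 h. The marks fit only at the closing instant of each period.
- *Elapsed days.* The follow-up section counts this way, since vital status "will be sought on Day 30 from randomisation". Day 2 would then be 48 h and Day 4 would be 96 h, but randomisation would have to stand under Day 0, and the table puts it under Day 1.
- *Time zero is the first dose.* A delay of 0 to 12 h moves the 48 h point to Day 3 or 4 and the 96 h point to Day 5 or 6. Day 2 never matches 48 h, and Day 4 never matches 96 h.

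**The case against.** The strongest reply is that the protocol never defines a day, so the calendar reading is the reader's choice. With 24-hour periods, 48 h closes the second day and 96 h closes the fourth, and the spacing between the two marks is right. On this view the fault is an undefined label, not a contradiction. The reply is fair as far as it goes, but it needs every draw to be taken at the last moment of the marked period. The alternative elapsed-day count needs a Day 0 that the table lacks. Neither convention is stated.

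A second reply is that the grid is only an overview. It marks Day 7, which the footnote leaves to clinical judgement, and the footnote sets a minimum, so an empty cell does not forbid a draw. That is true. Still, if the marks on Day 2 and Day 4 were extra draws, the compulsory ones on Day 3 and Day 5 should be marked as well, and Section 4.1 refers sites to this table for the schedule.

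A third reply concerns consequences, and most of it stands. The exact hours appear in the row's own footnote and in Section 4.1 itself, so a site would have to overlook both to be misled. The electronic case report form, which may label visits in hours, is not available to check. With no sampling window stated, nothing shows that a Day 2 or Day 4 draw would be rejected, so loss of data is conjecture. The 50% and 75% figures apply to a draw at the same clock time as randomisation, not to every draw.

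**Conclusion.** The point holds as a minor internal contradiction. The marks in Appendix 2 do not agree with the footnote to the same row or with the three other places that give the sampling hours. Because those four places agree with one another, the marks are what needs correcting, not the time points.

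The nominal error is 24 h at each of the two samples, for sites that follow the marks and draw at the clock time of randomisation. Across all clock times the draw falls between 0 and 48 h instead of at 48 h, and between 48 and 96 h instead of at 96 h. This rests on reading the column headings as calendar days with randomisation on Day 1, which is what the table shows.

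Only the secondary laboratory comparisons are exposed. The schedule is the same in both arms, so no between-arm bias is evident. The primary efficacy endpoint and the bleeding endpoints do not depend on these samples.

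**What to change.** In the laboratory row of Appendix 2, move the mark under Day 2 to Day 3 and label it 48 h, and move the mark under Day 4 to Day 5 and label it 96 h. Alternatively, label the relevant columns in hours from randomisation. Keep the 48 h and 96 h time points themselves. Send the sites a short note saying that the hours in the footnote govern.

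The cost is two marks or two column labels and one notice to sites. The number of blood draws is unchanged. Since the stated sampling hours do not change, the memorandum route that Section 6.1 gives for minor clarifications appears to be open.

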**APPENDIX 5: flow-chart**

**
[figure not shown]
**
